### Primary outcomes

The Pittsburgh Sleep Quality Index (PSQI), comprising 19 self-rated and 5 hetero-rated items, will be employed to evaluate the primary outcome of global sleep quality over the past month across 7 components: sleep duration, sleep latency, sleep efficiency, sleep medication use, sleep disturbances, subjective sleep quality, and daytime dysfunction. PSQI will be assessed at baseline, after each 4-week treatment phase (weeks 4, 8, 12), and during follow-up at weeks 16 and 24.

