### Sample size

The Pittsburgh Sleep Quality Index (PSQI) score following the full acupuncture intervention regimen was utilized to determine the requisite sample size. Statistical significance was defined as α = 0.05 with a power of 90%. Based on a prior study, perimenopausal women with insomnia had mean±SD PSQI scores of 11.43±2.11 with sham acupuncture and 9.20±3.24 with manual acupuncture [30]. Using the sample size formula:

$$n=2\times {\left[\;\frac{\left(Z_{\alpha }+Z_{\beta }\right)\times \sigma }{\delta }\;\right]}^{2}$$

Using the larger standard deviation of 3.24, with δ = 11.43–9.20 = 2.23, β = 0.1, 1-β = 0.9, and α = 0.05. The resultant sample size required per group was 44. Allowing for a 20% loss to follow-up, the total sample size needed for the study was 110 participants.

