### Statistical analysis

Group allocation will be concealed from the statistician. All randomized participants will be included in the intention-to-treat (ITT) analysis, regardless of study completion status. To ensure accuracy, double data entry will be performed. Statistical analyses will be conducted using SPSS 24.0. Continuous variables will be summarized as mean ± standard deviation or median (interquartile range). Between-group comparisons will utilize two-sample t-tests or Wilcoxon signed-rank tests for skewed data. Within-group baseline to endpoint changes will be analyzed by repeated measure analysis of variance (ANOVA), with a primary focus on assessing interactions between groups and time. Categorical variables will be compared using Fisher’s exact or Chi-square tests. Statistical significance will be defined as p<0.05.

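### Baseline PSQI is collected but no stated analysis adjusts for it; ANCOVA on baseline would cost one degree of freedom and gain precision

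*Protocol article*

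**What the plan says.** The Primary outcomes section makes PSQI the primary outcome and gives six assessments: "PSQI will be assessed at baseline, after each 4-week treatment phase (weeks 4, 8, 12), and during follow-up at weeks 16 and 24".

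The Sample size section bases the calculation on the score after treatment, not on change from baseline: "The Pittsburgh Sleep Quality Index (PSQI) score following the full acupuncture intervention regimen was utilized to determine the requisite sample size". The planning values come from a prior study: "mean±SD PSQI scores of 11.43±2.11 with sham acupuncture and 9.20±3.24 with manual acupuncture". The calculation then uses the larger SD: "Using the larger standard deviation of 3.24, with δ = 11.43–9.20 = 2.23, β = 0.1, 1-β = 0.9, and α = 0.05". It arrives at 44 per group, and at 110 in total after a 20% allowance for loss.

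The Statistical analysis section names two analyses that cover continuous outcomes, PSQI among them:

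- Between groups: "Between-group comparisons will utilize two-sample t-tests", or a rank test when data are skewed.
- Over time: "Within-group baseline to endpoint changes will be analyzed by repeated measure analysis of variance (ANOVA"), with the main emphasis on the interaction of group with time. Baseline enters this model as one level of the outcome.

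Neither analysis takes the baseline value as a covariate. No baseline-to-outcome correlation and no baseline SD are given.

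**The concern.** Two features of the named analyses leave information unused.

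First, a t-test of the post-treatment score ignores baseline PSQI. Randomisation is in blocks of 10, and the article describes no stratification by baseline score. With about 44 analysed per arm, a chance difference at baseline can carry into the estimated effect to the extent that baseline predicts outcome.

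Second, the interaction that the section emphasises is a different quantity from the one on which the trial was sized. Reduced to baseline versus week 12, it compares mean changes. The variance of a change depends on the baseline-to-outcome correlation, and the sample size calculation has no such term. At low correlation that test has less power than the post-treatment comparison.

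At stake are the precision of the primary estimate and, for a change-type analysis, whether the intended 90% power is reached.

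**Working it through.** **Inputs from the Sample size section.** Difference δ = 2.23, SD 3.24 (the other group's SD is 2.11), α = 0.05, power 90%, 44 evaluable per group. Sidedness is not stated.

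**Assumptions, not in the document.** The correlation ρ between baseline and week-12 PSQI, varied over a range, and the baseline SD, first taken equal to the week-12 SD.

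**1. Reproduce the plan's figure.** n = 2 × [(1.960 + 1.282) × 3.24 / 2.23]² = 44.36, which the protocol gives as 44. A one-sided α would give 36.2, so the calculation is two-sided. 44 / 0.8 = 55 per arm, or 110 in total.

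**2. Effective SD of each analysis (equal SDs σ).**

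- Post-treatment t-test: σ
- Change score: σ√[2(1 − ρ)]
- ANCOVA on baseline: σ√(1 − ρ²)

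ANCOVA uses the baseline coefficient that minimises the residual variance. The t-test fixes that coefficient at 0 and the change score fixes it at 1, so neither can have a smaller variance. ANCOVA's only cost is one degree of freedom: near ρ = 0 its variance is about 1% higher than the t-test's.

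**3. Power at 44 per arm, σ = 3.24** (noncentral t, two-sided 0.05, one degree of freedom charged to ANCOVA):

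| ρ | t-test | Change score | ANCOVA |
|---|---|---|---|
| 0.2 | 89.1% | 71.3% | 90.3% |
| 0.3 | 89.1% | 77.0% | 91.7% |
| 0.4 | 89.1% | 83.0% | 93.6% |
| 0.5 | 89.1% | 89.1% | 95.8% |

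For example, at ρ = 0.3 the change-score SD is 3.24 × √1.4 = 3.83 and the ANCOVA SD is 3.24 × √0.91 = 3.09.

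**4. Where the change score loses to the post-treatment score.** With unequal SDs, Var(change) = SD_w12² + SD_base² − 2ρ·SD_base·SD_w12. This exceeds SD_w12² when ρ < SD_base / (2 × SD_w12). With equal SDs the break-even is 0.5. With an illustrative baseline SD of 2.11 it is 2.11 / 6.48 = 0.33, and at ρ = 0.4 the change SD is 3.08 and power is 92%.

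**5. Sensitivity to the planning SD.** The pooled SD is √[(2.11² + 3.24²)/2] = 2.73. With it, t-test power at 44 per arm is 97%. Change-score power, again with equal SDs, is 85%, 89%, 93% and 97% at ρ = 0.2, 0.3, 0.4 and 0.5. It is below 90% only at a correlation of about 0.3 or lower.

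**6. All six visits kept in the interaction.** The test is then an omnibus F-test with five numerator degrees of freedom, and the change-score figures do not apply to it. Under compound symmetry, SD 3.24 and 44 per arm, a constant post-baseline effect gives 77.8% at ρ = 0.3 and 91.3% at 0.5. An effect that builds to week 12 and then fades gives 62.3% and 79.1%. These figures rest on the assumed effect profile as well as on ρ.

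**The case against.** The strongest reply is that nothing here is an error. The trial was sized on the post-treatment score with its raw SD, and a two-sample t-test of that score is the matching analysis. It is valid under randomisation and gives 89% power at 44 per arm, or 95% if all 55 per arm are analysed. That stands: this is a point about efficiency, not about bias or a wrong sample size.

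A second reply is that covariates are often left to the statistical analysis plan, and that the section does not tie the t-test to PSQI by name. This stands in part. The tests are named in the protocol, however, and their wording covers between-group comparisons of continuous variables, PSQI included. A later plan would have to replace this choice and not merely add detail.

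Three stronger readings are tempting, and the document supports none of them:

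- A reader might infer that the stated interaction test is underpowered. That needs a low correlation. The change-score figures also need a reduction to two visits, equal SDs and the larger planning SD; the shortfall narrows or disappears when these are relaxed.
- A reader might take 0.5 as the general threshold for the correlation. It holds only if the baseline and week-12 SDs are equal.
- A reader might argue that entry at PSQI above 5 guarantees a prognostic baseline. An entry floor restricts the range and could lower the correlation. A low correlation also shrinks the ANCOVA gain, to about 1 point at 0.2.

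**Conclusion.** The point holds as an improvement that costs almost nothing, not as a defect in the sizing. The named t-test delivers essentially the planned power. ANCOVA on baseline protects the estimate against chance baseline imbalance. At 44 per arm with SD 3.24 it adds about 3 to 7 percentage points of power at correlations of 0.3 to 0.5, and nothing near 0. The gain is smaller with the pooled SD, where the t-test already has 97%.

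The change-type analysis can fall short of 90%, but only under stated conditions: a correlation below about 0.5 with equal SDs of 3.24, or about 0.3 or lower with the pooled SD. Because neither the correlation nor the baseline SD is documented, the size of any loss cannot be fixed from the protocol. The preference for ANCOVA does not depend on those values, apart from the one degree of freedom.

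**What to change.** State the primary analysis as an ANCOVA of week-12 PSQI on treatment group and baseline PSQI. A mixed model with baseline PSQI as a covariate and the week-12 between-group contrast as the primary comparison serves equally well. Report the adjusted mean difference with its 95% confidence interval. Analyse the other continuous outcomes that have a baseline value in the same way, each with its own baseline: SAQ, SF-36, HAMD, GAD-7 and the blood biomarkers (on a log scale if skewed).

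The cost is a change of wording and one degree of freedom. No further data are needed and N stays at 110. The Trial status section describes recruitment as under way, so the change should be made and dated before the database is locked and the allocation is revealed.

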### Randomization procedure and allocation concealment

In this trial, block randomization will be employed with a block size of 10. The research coordinator will generate randomization numbers independently utilizing SPSS 24.0 software without contacting study participants. To ensure allocation concealment, sequentially numbered opaque sealed envelopes will be employed, with an assigned designee independently administering the randomization sequence. Subsequent to informed consent, a total of 110 patients will be randomly allocated in a 1:1 ratio to the treatment arm (acupuncture group) or the control arm (sham acupuncture group).

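### The skewness rule for between-group tests makes no exception for PSQI, so the observed data can decide whether the primary comparison tests the mean difference the trial was sized on

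*Protocol article*

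**What the plan says.** The protocol article's Statistical analysis section sets a single rule for continuous outcomes: "Between-group comparisons will utilize two-sample t-tests or Wilcoxon signed-rank tests for skewed data". It gives no criterion for skewness and does not treat PSQI separately. The same section then names a repeated-measures ANOVA. This is introduced for change within groups, but its stated main interest is the group-by-time interaction.

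The Sample size section works entirely in means. It bases the calculation on PSQI after the full course of acupuncture, which is week 12. From a prior study it takes "11.43±2.11 with sham acupuncture and 9.20±3.24 with manual acupuncture", sets "δ = 11.43–9.20 = 2.23", and proceeds "Using the larger standard deviation of 3.24". The outcome is stated as "The resultant sample size required per group was 44", and then "Allowing for a 20% loss to follow-up, the total sample size needed for the study was 110 participants". Allocation is 1:1, so this is 55 per arm.

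The signed-rank test is a paired test and does not fit two independent arms. The two-sample rank-sum (Mann-Whitney) test is presumably meant, and it is used below, so this point does not depend on the misnaming.

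**The concern.** A t-test and a rank-sum test answer different questions. The t-test concerns the difference in means. The rank-sum test concerns the probability that a woman in one arm scores lower than a woman in the other, counting ties as half. The two coincide as tests of location when the arms share shape and spread. When they do not, that probability can differ from one half although the means are equal.

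The prior study cited for sizing had clearly unequal spread: the SD ratio is 3.24/2.11 = 1.54 and the variance ratio 10.50/4.45 = 2.36. If acupuncture helps only some women, the acupuncture arm would be both wider and skewed, and skew is what triggers the switch. The primary p-value could then refer to something other than the 2.23 points, and its error rate for equal means could move away from 5%.

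**Working it through.** **1. The plan's own figure.** Inputs from Sample size: α = 0.05, power 90%, σ = 3.24 in both arms, δ = 2.23.

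n = 2 × [(1.960 + 1.282) × 3.24 / 2.23]² = 44.36 per group.

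The stated 44 is reproduced (rounded down) with a two-sided α; a one-sided α would give 36.2. Dropout: 44/0.8 = 55 per arm, 110 in total. The sizing is therefore for a difference in means.

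**2. Error rate when means are equal.** Simulation with 10,000 to 20,000 trials per setting, 44 and 55 per arm. Scores are normal or shifted gamma, rounded and limited to 0-21, with both means 10.3. The switch goes from t-test to rank-sum if a skewness test or Shapiro-Wilk gives p < 0.05 in either arm. The article gives neither the skewness nor the trigger; both are assumptions. Ranges run over both sample sizes and, for the switch, both triggers.

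| SDs (acupuncture, sham) | Assumed skew | Welch, fixed | Switch |
|---|---|---|---|
| 3.24, 2.11 | none (normal) | 4.9% | 5.1-5.3% |
| 3.24, 2.11 | 0.5 in both arms | 4.9-5.0% | 5.7-6.0% |
| 3.24, 2.11 | 1 in both arms, same direction | 4.9-5.5% | 7.9-8.9% |
| 3.24, 2.11 | 1 in the wider arm only | 4.8-4.9% | 8.9-10.3% |
| 3.24, 2.11 | 1.5 in both arms | 5.1% | 12.2-13.6% |
| 3.24, 2.11 | 1, opposite directions | 5.3-5.7% | 12.4-14.4% |
| 3.24, 3.24 | 0 to 1.5 in both arms | 4.7-5.2% | 4.6-5.3% |

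The excess needs skew and unequal spread together. At skew of 1 or more it is larger with 55 per arm than with 44. If the narrower arm is the more skewed one (0.8 and 1.23, or 0.5 and 0.77), the rank-sum test alone gives 5.7-7.0%.

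**3. A responder pattern.** 8,000 trials per setting, 44 per arm, sham SD 2.11. The acupuncture arm is a mixture with 20%, 25% or 30% responders, gaps of 6.5, 6 or 5.5 points, and component SD 2.0. Its SD is √(2.0² + p(1−p)·gap²):
- 20%: √(4 + 0.16 × 42.25) = 3.28
- 25%: √(4 + 0.1875 × 36) = 3.28
- 30%: √(4 + 0.21 × 30.25) = 3.22

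The skew is −0.4 to −0.7. With equal means, Welch rejects in 4.7-5.6% of trials and the Shapiro-Wilk switch in 7-12%.

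**4. Power for 2.23 points.** In the responder settings at 44 per arm, Welch has 97% and the switch 92-93%. With normal or gamma scores, SDs 3.24 and 2.11 and 44 per arm, Welch has about 96-97% and the rank-sum test 95.6% or more. With SD 3.24 in both arms, the fixed t-test has 89.8% at 44 and 95.0% at 55.

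**The case against.** Several stronger readings are tempting, and the document does not support them.

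- **That unequal spread alone breaks the 5% level.** It does not: normal data with SDs 3.24 and 2.11 give 5.1-5.3%. Skew is also needed, and the article gives none for PSQI.
- **That an inert treatment would be declared effective too often.** If acupuncture does nothing and the arms share one distribution, the switch stays near 5%. The excess arises only when the distributions differ while the means are equal. In the responder settings this requires non-responders to sit 1.3, 1.5 or 1.65 points (share × gap) worse than sham, and nothing in the article suggests that. The excess is therefore a statement about which quantity is tested.
- **That the plan expects unequal spread.** It reports the prior study's SDs but sizes with 3.24 in both arms.
- **That power is lost to a harmful degree.** Even the lowest switched power, 92-93%, is above the planned 90%.
- **That the switch is declared as the primary PSQI test.** The sentence is general. It also covers the blood biomarkers, where a rank option is ordinary, and the ANOVA beside it is mean-based with no skewness switch and could be meant as the main analysis. That the rule governs PSQI is the natural reading, since between-group comparisons are assigned to it without exception, but it is not explicit.
- **That the team would pick the smaller p-value.** The article describes no such practice and conceals allocation from the statistician. With identical distributions that practice would give 5.9%.

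A statistical analysis plan that is not shown may define skewness and the effect estimate, so their absence is not held against the article. What stands is that the published rule, as worded, makes the test depend on the data for the outcome on which the trial was sized. Blinding the statistician does not change which hypothesis is tested.

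**Conclusion.** The point holds as a conditional one. As the general rule is written, the observed distribution can move the primary week-12 PSQI comparison away from the difference in means used for sizing. That change of question occurs whenever the switch fires and the arms differ in spread or shape; it does not depend on the simulations.

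The size of the error-rate effect does depend on assumptions. Under the prior study's SDs and an assumed absolute skew of 0.5 to 1.5, equal means are rejected in about 6% to 14% of trials, against about 5% for a fixed Welch test. Without skew, without unequal spread, or with identical distributions, there is no material excess. The sample size needs no change.

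**What to change.** For PSQI, replace the general rule with one week-12 comparison of means, fixed in advance and allowing unequal variances: a Welch test, or a linear model with robust standard errors. Report it as a mean difference with 95% CI whatever the observed skew. Report a two-sample rank-sum test, correctly named, as a sensitivity analysis only. State how this comparison relates to the repeated-measures ANOVA, so that it is clear which result is primary. The general rule may remain for other outcomes once the test is correctly named.

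The cost is a sentence or two of analysis wording, agreed before unblinding, with no extra data or patients. The team gives up choosing the PSQI test after seeing the data.

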### Secondary outcomes

Assessment of stable angina pectoris (SAP): SAP was evaluated at baseline, week 4, week 8, and week 12 using the Seattle Angina Questionnaire (SAQ) to quantify angina symptoms before and after treatment. Blood biomarkers of SAP: Fasting venous blood samples were collected from the cubital fossa on the start and final of the treatment period in both groups. Levels of C-reactive protein (CRP), lipoprotein-associated phospholipase A2 (Lp-PLA2), and cardiac fatty acid-binding protein (C-FABP) were assayed by an independent laboratory blinded to group allocation.Quality of life assessment using the 36-Item Short Form Health Survey (SF-36).Dosage of sleeping pills.Hamilton Depression Rating Scale (HAMD).Generalized Anxiety Disorder 7-item (GAD-7) scale.

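### The repeated-measures ANOVA of baseline-to-endpoint change has no provision for skewed data, so if CRP, Lp-PLA2 and C-FABP are analysed as measured, power is lost to the extent that they are right-skewed

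*Protocol article*

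**What the plan says.** The Secondary outcomes section of the protocol article lists CRP, Lp-PLA2 and C-FABP as blood markers of stable angina and fixes when they are taken: "Fasting venous blood samples were collected from the cubital fossa on the start and final of the treatment period in both groups". Each woman therefore contributes one value before treatment and one after.

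The Statistical analysis section has three provisions for continuous variables:

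- **Summaries:** mean and SD, or median and interquartile range.
- **Between-group comparisons:** a two-sample t-test or, where data are skewed, a Wilcoxon signed-rank test.
- **Change from baseline:** "Within-group baseline to endpoint changes will be analyzed by repeated measure analysis of variance (ANOVA), with a primary focus on assessing interactions"; the interaction meant is group by time.

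The third provision names no outcome, no scale and no alternative for skewed data. The sample size rests on the PSQI alone ("The resultant sample size required per group was 44"). The article states no SD, effect size or power for any biomarker.

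**The concern.** The section foresees skewed variables but covers them in only one of its two inferential analyses. The analysis of change, where the group-by-time interaction is the term of interest, is left uncovered.

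For an outcome measured twice in two groups, that interaction is the same test as a two-sample t-test on the change score. If a concentration is right-skewed and treatment lowers it by a proportion, women with high values have large absolute changes and the rest have small ones. The spread of the raw changes then grows faster than the difference between arms, and power falls. On the log scale a proportional effect is a constant shift and this does not happen.

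At stake is how the biomarker results can be read. With the SAQ, these markers make up the stable-angina outcomes. The trial was not sized on them, so they have no designed power margin. A transformation chosen after the data are seen would also be open to challenge.

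**Working it through.** **1. Sample size, to fix n per arm.** Inputs from the Sample size section: "Using the larger standard deviation of 3.24, with δ = 11.43–9.20 = 2.23, β = 0.1, 1-β = 0.9, and α = 0.05". With two-sided α, n = 2 × [(1.96 + 1.2816) × 3.24 / 2.23]² = 2 × 4.710² = 44.36, against the stated 44. For losses: 44 / (1 − 0.20) = 55 per arm, 110 in total, as stated. The figure reproduces, concerns the PSQI only, and gives 44 per arm as the number expected to complete.

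**2. What the interaction tests.** With two times and two groups, the interaction contrast is (post − pre) with acupuncture minus (post − pre) with sham. Its test is the two-sample t-test on change. The choice of scale is therefore raw change against log change.

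**3. Assumptions, none of them from the article.** Log-normal values; correlation of 0.7 between start and end on the log scale; a true 30% reduction with acupuncture; 44 per arm; log-scale SD varied from 0.2 to 1.2.

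**4. Log-scale power in closed form, as a check.** The effect is ln(0.70) = −0.357. The SD of log change is s × √[2(1 − 0.7)] = 0.775s. The standard error of the difference is 0.775s × √(2/44) = 0.165s. At s = 1.0 the ratio is 0.357 / 0.165 = 2.16, and power is about Φ(2.16 − 1.96) = Φ(0.20) = 58%. At s = 0.5 the ratio is 4.32, and power is about Φ(2.36) = 99%. Both agree with the simulation.

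**5. Simulated power, t-test on raw change versus log change.**

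| Log-SD (assumed) | Raw scale | Log scale | Relative loss |
|---|---|---|---|
| 0.2-0.3 | essentially 100% | essentially 100% | none |
| 0.5 | 93% | 99% | (99 − 93)/99 = 6% |
| 0.8 | 47% | 76% | (76 − 47)/76 = 38% |
| 1.0 | about 28% | 58% | (58 − 28)/58 = 52% |
| 1.2 | 17% | 43% | (43 − 17)/43 = 60% |

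Repeating the simulation moves these powers by at most about 3 points. With correlation 0.5 and log-SD 1.0, power is 19% raw against 38% log. The false-positive rate is about 5% on the log scale and 4-5% on the raw scale, so the gain does not come from inflated error.

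**6. Sensitivity to the effect size.** The 30% effect gives near-certain detection at small SD, which could hide a loss. The effect was therefore also set, at each SD, to give about 80% power on log change, with 44 or 55 per arm and correlation 0.5 or 0.7. The relative loss on the raw scale was 4-5% at log-SD 0.2, 7-8% at 0.3, 17-18% at 0.5, 36-38% at 0.8, 47-50% at 1.0 and 59-60% at 1.2. The direction is the same throughout, and the loss is small where skew is mild.

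**7. Whether the existing rank-test route makes up the loss.** Take it as an independent-samples rank test on end-of-treatment values, with log-SD 1.0 and a 30% reduction. At correlation 0.5 it has about 35-36% power, against 38-39% for log change and 19-20% for raw change. At correlation 0.7 it has 36-40%, against 55-58% for log change. It recovers most of the loss in the first case and only part in the second.

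**The case against.** **The scale is not stated.** The article never says the ANOVA uses untransformed values, and a condensed article may leave transformation to an analysis plan that is not shown. A reader might infer that raw-scale analysis has been specified. The text does not support that: it is silent on scale. What survives is narrower. The section does address skewness, ties its rank test to one analysis only and leaves the other with none, so the raw scale is the plain reading of what is written.

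**What the stated focus means.** A reader might infer that the ANOVA is the primary analysis of every outcome. The sentence ranks the interaction above the other terms within the ANOVA. It does not rank the ANOVA above the between-group comparisons.

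**Skew has a route already.** This stands in part. A rank comparison at the end of treatment would recover much of the loss when the two measurements are only moderately correlated. However, the signed-rank test named is a paired test and does not fit two independent arms, and the route does not extend to the analysis of change.

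**The premises are external.** This stands. No distribution is given for any of the three markers, and they may differ. A reader might infer that a few high values will dominate all three results, or that power falls by up to about half. Neither follows: the loss is nil to small at log-SD 0.2-0.3 and about 60% at 1.2, so one half is the result at a single assumed SD near 1.0. Nor is a null raw-scale result always uninformative. At log-SD 0.5 the raw analysis has 93% power, while at 1.0-1.2 the log analysis itself has only 58-43%.

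**Visit schedule.** The Abstract has secondary outcomes assessed at baseline, weeks 4, 8 and 12 and follow-up, whereas the Secondary outcomes section gives two blood samples. The more specific section is used here. With more visits the equivalence to a t-test on change would no longer be exact, and the figures above would not carry over directly.

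**Conclusion.** The point holds as a minor one. The skewness provision does not reach the ANOVA of baseline-to-endpoint change. Run on raw concentrations, that analysis would remain valid but could be inefficient for CRP, Lp-PLA2 and C-FABP. The cost ranges from nothing to about 60% of the log-scale power. It depends on the log-scale SD, which the documents do not give, and on log-normality, a proportional effect and the correlation between the two samples, all of which are assumed. Only secondary outcomes are affected. The PSQI analysis, its sample size and the other questionnaire scores are not.

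**What to change.** Add one sentence to Statistical analysis: CRP, Lp-PLA2 and C-FABP are natural-log transformed before the repeated-measures ANOVA or any t-test, and the treatment effect is reported as a ratio of geometric means with 95% CI. Keep the PSQI, SAQ, SF-36, HAMD and GAD-7 on their own scales. In the same edit, replace the signed-rank test in the between-group sentence with the rank-sum test for independent groups.

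The cost is small. No further data or participants are needed. Biomarker results would be read as percent differences instead of concentration units, and a marker that proves only mildly skewed gains little. The sentence should be fixed before any outcome data are seen.

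### The sample size powers a single end-of-treatment PSQI comparison, but the analysis gives primary focus to a group-by-time interaction and no primary time point is fixed, so the 90% power is unverified for the emphasised test

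*Protocol article*

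**What the plan says.** Three sections of the protocol article bear on this point.

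- **Sample size:** "The Pittsburgh Sleep Quality Index (PSQI) score following the full acupuncture intervention regimen was utilized to determine the requisite sample size". The calculation is a two-group comparison of means with α 0.05, power 90%, a difference of 2.23 and SD 3.24. It gives 44 per group, and 110 in total after a 20% loss allowance. The Interventions section sets 36 sessions over 12 weeks, so the powered time point is week 12.
- **Primary outcomes:** "PSQI will be assessed at baseline, after each 4-week treatment phase (weeks 4, 8, 12), and during follow-up at weeks 16 and 24". No visit is singled out as primary.
- **Statistical analysis:** between-group comparisons use two-sample t-tests or a rank test, with no visits named. Repeated-measures ANOVA is introduced for within-group change from baseline to endpoint, "with a primary focus on assessing interactions between groups and time". One rule covers everything: "Statistical significance will be defined as p<0.05".

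**The concern.** A week-12 difference in means and a group-by-time interaction are different hypotheses. The first has a direction and gives an effect in PSQI points at a defined time. An interaction over more than two visits is an omnibus test with no direction. If follow-up visits enter, it combines the treatment period with the period after treatment stops. It can then be significant because of an early transient difference or a rebound after treatment, and it can miss a real week-12 benefit.

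Two things are at stake. The power quoted for the trial may not be the power of the test on which its conclusion rests. And with no primary contrast named, it is open which PSQI result decides whether the trial is positive.

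**Working it through.** **1. The plan's own figure.** Inputs from the Sample size section: "δ = 11.43–9.20 = 2.23", σ = 3.24, α = 0.05, power 0.90. The formula given there is n = 2[(Zα + Zβ)σ/δ]².

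- Two-sided: 2 × [(1.960 + 1.282) × 3.24/2.23]² = 44.36 per group. The stated 44 matches within rounding.
- One-sided: 36.16. The plan therefore used a two-sided 0.05.
- Loss allowance: 44/0.8 = 55 per group, 110 in total, as stated.
- Power of a week-12 t-test at 44 per arm: noncentrality 2.23/(3.24 × √(2/44)) = 3.228 on 86 df, which gives 89.1% (89.8% by the normal approximation).

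The calculation is sound for a single two-sided week-12 comparison.

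**2. Power of the interaction test.** The article gives neither the within-person correlation ρ of PSQI nor the effect at visits other than week 12. Assumptions: compound symmetry, SD 3.24 at every visit, ρ from 0.3 to 0.7, no baseline difference and an effect of 2.23 at week 12. For k visits with between-arm differences cⱼ, the F test has k − 1 and (k − 1)(2n − 2) df, and noncentrality

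λ = n Σ(cⱼ − c̄)² / [2σ²(1 − ρ)].

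With n = 44:

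| Reading and effect profile | Σ(cⱼ − c̄)² | df | ρ = 0.3 | ρ = 0.5 | ρ = 0.7 |
|---|---|---|---|---|---|
| Six visits, waning: 0, 0.74, 1.49, 2.23, 1.49, 0.74 | 3.04 | 5, 430 | 62% | 79% | 96% |
| Six visits, sustained: 0, then 2.23 at all five | 4.14 | 5, 430 | 78% | 91% | 99% |
| Baseline and week 12 only: 0, 2.23 | 2.49 | 1, 86 | 77% | 89% | 98.5% |

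Example, first row at ρ = 0.3: λ = 44 × 3.04/(2 × 10.50 × 0.7) = 9.1, power 62%. The abstract's schedule has no week-16 visit. Dropping that visit moves the six-visit figures by less than two percentage points.

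**3. Type I error.** One prespecified test at 0.05 keeps 5% (for the interaction, if sphericity holds or is corrected). Suppose instead that significance at any of the five post-baseline visits counted as success. The chance of at least one false positive would be 1 − 0.95⁵ = 22.6% for independent tests. By simulation with equally correlated statistics it is 20.9%, 18.4% and 14.8% at correlations 0.3, 0.5 and 0.7.

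**4. Power of a baseline-adjusted week-12 comparison.** Adjusting for baseline PSQI multiplies the SD by √(1 − ρ²), so the noncentrality is 2.23/(3.24 × √(1 − ρ²) × √(2/44)) on 85 df. This is 3.38, 3.73 and 4.52 at ρ = 0.3, 0.5 and 0.7, giving 92%, 96% and 99%.

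**The case against.** The strongest reply is that this is a condensed article. The exact primary model, its visits and the order of testing are commonly left to an analysis plan that is not shown, and the Sample size section already points to PSQI after the full regimen. That would answer a complaint of missing detail. It does not answer this point, because the article states where its primary focus lies, and that is not expressly the quantity it powered.

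A reader might go further and infer that the 90% power fails. The documents do not support that. The ANOVA sentence names no visits, and six is an inference from the assessment schedule. On a baseline-versus-week-12 reading, the interaction is simply the t-test on change at the powered time point. The 62% pairs the lowest correlation tried with a waning effect, and other plausible inputs exceed 90%. Also, 44 per arm is the number after losses, while the intention-to-treat analysis includes all randomised participants. With 55 per arm and no losses, the waning profile gives 74%, 88% and 99%, and the sustained profile 88%, 97% and 99.9%. Interaction power may thus lie on either side of 90%.

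A reader might also infer that the 5% error rate is lost through testing at every visit. The article does not say that t-tests are run at each visit, or that any visit may count as success. The t-test sentence is generic and can equally cover baseline and secondary variables.

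**Conclusion.** The concern holds as a mismatch between the powered quantity and the emphasised test, together with the lack of a primary PSQI time point. The sample size itself reproduces and is adequate for a week-12 comparison (about 89-90%). For the interaction, the 90% is unverified: about 62% to 99% if six visits enter, and 77% to 98.5% if only baseline and week 12 do. Both ranges rest on 44 per arm, SD 3.24, compound symmetry and correlations of 0.3 to 0.7, and the six-visit range also on assumed effect profiles. The 15-21% error rate is conditional on an any-visit success rule that the protocol does not state and does not exclude. The Trial status section says recruitment is under way, so the contrast should be fixed before any unblinded results are seen.

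**What to change.** Name one primary test: the between-arm difference in PSQI at week 12, adjusted for baseline PSQI, two-sided at 0.05, reported with a 95% confidence interval. This is the quantity the sample size was built on, and it does not depend on what happens after treatment stops. Make PSQI at weeks 4, 8, 16 and 24 and the overall group-by-time interaction secondary, with no efficacy claim resting on them.

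The cost is wording in the protocol, the analysis plan and the registry entry. No extra patients, visits or data are needed. The downside is that no primary claim can rest on the follow-up visits. If the interaction is to stay primary, the sample size should be recalculated for it, with the visits, the correlation and the effect profile stated.
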